#### Teachers’ Measures

Table 4 [45,50] shows the list of measures that teachers will complete about their children.

**Table 4 table4:** List of measures that teachers will complete about children.

Name of the scale	Brief description	Style of administration
The Strengths and Difficulties Questionnaire [45]	The questionnaire asks about the teacher’s report on students’ emotional symptoms, conduct problems, hyperactivity/inattention, peer relationship problems, and prosocial behavior.	Pen and paper
Amended: Questionnaire about school resources for mental health support [50]	The questionnaire will ask about all the different resources available to students that are provided by the school for mental health support. Questions about creative arts therapies have been added.	Online platform

### Data Analysis

#### Planned Analyses

This study will explore the association between mental health and resilience in primary school children while assessing the impact of the psychological factors, social factors, and resources available to them. We will also assess the resilience scores in this age group, the psychometric properties, and how these scores might predict mental health problems in relation to the psychological factors, social factors, and resources available. As our dataset will contain multiple possible combinations of the predictors and different ways of operationalizing resilience (even across time), more specific hypothesis-driven analysis will be individually preregistered on the Open Science Framework website prior to any analysis. A key analysis will include assessing the impact of the opt-in versus opt-out recruitment process on systematic selection bias. Where relevant and if this overall analysis is significant, we will include this as a sensitivity analysis on a paper-by-paper basis, and this will be stated in the analysis preregistration.

To assess the feasibility (uptake, retention) of developing a longitudinal cohort study of preadolescent children in East London, we will record information on our school recruitment process: (1) number of schools contacted, (2) number of schools who responded with interest, (3) number of schools who had an initial meeting with us, (4) number of schools where we reached out to parents/carers, (4) number of schools where we reached out to children, (5) number of children we spoke to, (6) number of parents/carers who provided consent, (7) number of children who provided assent, (8) number of children who completed at least one assessment, (9) number of parents/carers who completed at least one assessment, and (10) mean number of assessments completed.

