#### Consenting Process

Prior to enrolment, research assistants conducted an in-school talk aimed at children from the targeted age group about the DEER study. After the talk, they distributed information sheets to children and their parents/carers. Initially the ethics committee recommended that the consenting process be opt in, that is, in addition to assent collected from children, parents or guardians needed to provide written consent in order for a child to take part. When it became apparent that enrolment was very low (by November 2022, only 6.9% (131/1898) of the consent forms were returned signed) and potentially biased in favor of parents and families who were better resourced, the ethics committee allowed for an opt out process. This means that for the 10 recruited schools, 6 are opt-in only, 1 began with opt-in processes but then agreed to participate using opt-out procedures, and the remaining 3 are opt-out only schools. For opt-out schools, parents were asked to return a form or contact the school or research team to indicate they did not want their child to take part, and then no data were collected from the opted-out children. The team liaised with schools to ensure that only students who met our inclusion criteria were enrolled in the study. Because most of the data are self-reported, some of our measures are not suitable for students who have been diagnosed with an intellectual disability disorder.

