#### Sample Size

Based on the planned analyses, the target recruitment was 1200 children in school years 3-5 (age 7-11 years). This sample size provides (1) 94% power to detect correlations as small as 0.10 (2-tailed), *P*<.05 between resilience measures and correlates and (2) the opportunity to compare groups high and low on a psychological or social factors (eg, top and bottom 20% of the sample on attention control) or on a resilience measure and to detect even small effects (eg, Cohen *d*=0.30) at 90% power, 2-tailed, *P*<.05.

Importantly, this sample size will enable us to use novel data-driven analytic approaches to identify subpopulations with different resilience trajectories across time and to assess the predictive value of different psychosocial variables (main effects, interactions, mediation effects) on resilient trajectories by using multinomial logistic regression. This will also allow us to use other advanced quantitative analyses, including structural equation modelling (to explore mediation and moderation effects), a combination of exploratory and confirmatory factor analysis (to verify the factor structure of selected questionnaires), and network analysis to explore associations between individual items of questionnaires.

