## Results

Barts Charity awarded a grant to the Faculty of Medicine and Dentistry, Queen Mary University of London, on March 30, 2020, to establish the Youth Resilience Unit. The Unit was established on March 1, 2021. This core funding also provided support for this study. Ethics approval (QMERC22.251) was granted by the Queen Mary research ethics committee on June 27, 2022. Study recruitment commenced from October 2022 and continued till December 2023. Baseline testing commenced in October 2022 and continue till December 2023; 873 students were enrolled at baseline. Follow-up is anticipated to continue at least annually until June 2027. Baseline and follow-up questionnaires will provide evidence regarding the acceptability and feasibility of conducting a longitudinal cohort study in primary schools in East London.

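### The paper-level opt-in/opt-out sensitivity analysis should not depend on a significant overall comparison, because with 10 schools a non-significant result cannot rule out material selection bias

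*Protocol article*

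**What the plan says.** The Planned Analyses section of the protocol article commits to an overall assessment: "A key analysis will include assessing the impact of the opt-in versus opt-out recruitment process on systematic selection bias". That step is unconditional. The next sentence governs individual papers: "Where relevant and if this overall analysis is significant, we will include this as a sensitivity analysis on a paper-by-paper basis". The decision is then to be recorded in each paper's preregistration. Two conditions must therefore both be met, relevance and a significant overall result.

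The Consenting Process section describes how route was assigned among the 10 schools that took part: "6 are opt-in only, 1 began with opt-in processes but then agreed to participate using opt-out procedures, and the remaining 3 are opt-out only schools". The move to opt-out followed low uptake: by November 2022, "only 6.9% (131/1898) of the consent forms were returned signed", and the resulting enrolment was described as "potentially biased in favor of parents and families who were better resourced".

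The Results section reports that "873 students were enrolled at baseline", without a split by consent route. The power statement under Sample Size is for a target of 1200 children and covers correlations and high/low group contrasts. It does not cover the comparison of consent routes.

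**The concern.** A test of whether opt-in and opt-out children differ is being used to decide whether later papers examine consent route at all. Two things are wrong with that.

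First, failing to reject is not evidence of no difference. Apart from the one school that switched, route varies only between schools. The precision of the comparison is therefore governed by the number of schools, not the number of children.

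Second, the overall comparison answers a different question. Differences in who was recruited do not show whether a particular exposure-outcome association depends on route. Even a precise overall test would not settle that for a given paper.

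What is at stake is whether readers of each paper can see how far its result depends on recruitment. The authors changed the consent process partly because they suspected selection on family resources, and resources are among the factors the study sets out to relate to resilience.

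**Working it through.** **The protocol's own power figures.** At N = 1200 and r = 0.10, Fisher's z gives atanh(0.10) × √1197 − 1.96 = 0.1003 × 34.60 − 1.96 = 1.51, so power is 93.5% (the article states "94% power to detect correlations as small as 0.10 (2-tailed"). For the top and bottom 20%, n = 0.20 × 1200 = 240 per group. At d = 0.30, 0.30 × √(240/2) − 1.96 = 1.33, so power is 90.8% (stated 90%). Both figures reproduce, but both treat children as independent and neither concerns consent route.

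**Inputs for the comparison that acts as the switch**
- From the article: 873 children; 10 schools, divided 6/1/3.
- Assumed, because the article does not give them: two-sided alpha of 0.05; a school-level test; the switched school counted as opt-out (6 v 4, 8 degrees of freedom); ICC of 0.02, 0.05 or 0.10; opt-in share of the children between 15% and 60%.

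**Precision with equal school sizes.** Children per school = 873/10 = 87.3. The standard error of the difference, in SD units, is √[(ICC + (1 − ICC)/87.3) × (1/6 + 1/4)]. The 95% half-width is 2.306 × SE (t on 8 df).

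| ICC | SE | 95% half-width | Difference needed for 80% power |
|---|---|---|---|
| 0.02 | 0.114 | 0.26 | 0.37 |
| 0.05 | 0.159 | 0.37 | 0.51 |
| 0.10 | 0.214 | 0.49 | 0.69 |

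At ICC 0.05, an observed difference of exactly zero would still be compatible with a true difference of up to 0.37 SD in either direction.

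**Probability that the sensitivity analysis is triggered.** This uses the noncentral t on 8 df, with variance [1 + (m₁ − 1)ICC]/n₁ + [1 + (m₂ − 1)ICC]/n₂, where n₁ + n₂ = 873, m₁ = n₁/6 and m₂ = n₂/4. Ranges span the assumed opt-in shares.

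| True difference | ICC 0.02 | ICC 0.05 | ICC 0.10 |
|---|---|---|---|
| 0.20 SD | 0.27-0.34 | 0.18-0.20 | 0.12-0.13 |
| 0.30 SD | 0.52-0.64 | 0.34-0.38 | 0.22-0.24 |
| 0.50 SD | 0.92-0.97 | 0.72-0.79 | 0.50-0.54 |

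At ICC 0.01 the 0.30 SD figure rises to 0.63-0.80. Leaving the switched school out (6 v 3) lowers the 0.30 SD figure at ICC 0.05 to 0.29-0.33.

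**If the test ignored schools.** With 873 children treated as independent, the probability of significance is 0.56-0.84 at 0.20 SD and 0.89-0.99 at 0.30 SD. That test is not valid. At ICC 0.05 the design effect is 1 + (87.3 − 1) × 0.05 = 5.3. The nominal 1.96 then acts as 1.96/√5.3 = 0.85, which gives a true type I error of about 0.40.

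**The case against.** The strongest reply is that the rule touches little. The overall opt-in/opt-out assessment goes ahead regardless, and only its repetition in individual papers is conditional. Specific analyses are preregistered one by one, no main estimate changes, and nothing prevents a paper from adjusting for consent route. All of this is true and limits the weight of the point. It does not rescue the condition, because the stated rule is carried into each preregistration.

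A second reply is that a child-level test would usually be significant, and a false positive would merely produce an extra sensitivity analysis, which does no harm. That is fair. It means that suppression is mainly a risk under a test that respects schools. But a switch that works only because its error rate is wrong is not a reason to keep it.

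Third, some outputs, such as the body-mapping work or a questionnaire's factor structure, may have no estimate for which a route contrast makes sense. That stands, and it is why the relevance condition should stay.

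A reader might also take the 6.9% as final opt-in uptake. The documents do not support that. It is a count of returned forms at November 2022, and recruitment ran to December 2023. For the same reason, 131 cannot be read as the number of opt-in children enrolled; the opt-in shares used above are assumptions.

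**Conclusion.** The point holds in a limited form: significance of the overall comparison is the wrong criterion for deciding whether a relevant paper reports the consent-route sensitivity analysis. This does not depend on any assumed value. Non-significance with 6/1/3 schools cannot exclude material selection, and the overall comparison is not about any one paper's association.

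The size does depend on assumptions. For a 0.30 SD difference, under a school-level test of 6 v 4 schools, the analysis would be skipped with probability about 0.36-0.48 at ICC 0.02, 0.62-0.66 at 0.05 and 0.76-0.78 at 0.10 (one minus the figures in the working).

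It is tempting to conclude that the sensitivity analysis will usually be suppressed even when bias is real. The documents do not support that. They give no ICC, effect size or test, and the statement fails at a low ICC, for a difference of 0.50 SD, or under a child-level test. The 6 v 4 split is also a simplification of the 6/1/3 design. Nor do the documents show that selection bias occurred; the authors call it a possibility. The point is worth correcting, but it concerns a secondary analysis in an observational cohort.

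**What to change.** In Planned Analyses, delete the condition that the overall comparison be significant and keep the relevance condition. State that every paper whose estimate consent route could affect will report its main estimate alongside a consent-route sensitivity analysis (for example adjusted for route, or shown by route), with 95% confidence intervals that account for school, whatever the p-value of the overall comparison. Report the overall opt-in/opt-out comparison as differences with confidence intervals rather than as a gate, and say how the switched school is classified.

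The cost is one amended sentence and one extra supplementary row per relevant paper. The intervals will be wide because there are only about 10 schools. That should be stated plainly, since it is the actual limit on what the study can say about selection. Follow-up is expected to run to June 2027 and papers are preregistered individually, so the change can be adopted for papers not yet preregistered.

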#### Missing Data

Where data are missing, these will either be imputed, or the participant will be removed from the analysis as appropriate for the statistical test being conducted. Because this method will vary according to the nature of the hypotheses and the statistical tests being conducted for any one individual paper, it cannot be stated now, but this will be included in the Open Science Framework preanalysis registration as appropriate (on a paper-by-paper basis). As there is no source documentation for the measures collected directly onto tablets, data cannot be entered during quality assurance checks. Data entry rules will make it very difficult for data to be missed during entry.

## Results

Barts Charity awarded a grant to the Faculty of Medicine and Dentistry, Queen Mary University of London, on March 30, 2020, to establish the Youth Resilience Unit. The Unit was established on March 1, 2021. This core funding also provided support for this study. Ethics approval (QMERC22.251) was granted by the Queen Mary research ethics committee on June 27, 2022. Study recruitment commenced from October 2022 and continued till December 2023. Baseline testing commenced in October 2022 and continue till December 2023; 873 students were enrolled at baseline. Follow-up is anticipated to continue at least annually until June 2027. Baseline and follow-up questionnaires will provide evidence regarding the acceptability and feasibility of conducting a longitudinal cohort study in primary schools in East London.

## Discussion

### Overview

Resilience is the ability to overcome adverse events and experience positive outcomes. Although the development of emotional resilience has been explored in adolescence, there is a dearth of evidence on the nature of and development of resilience among preadolescent populations.

The DEER study aims to explore how preadolescent children define resilience, track the development of resilience, and asses the contributory factors to differences in resilience pathways across time. It is hoped that the results of our study will allow us to work on more developmentally sensitive theories of resilience and propose future interventions to reduce negative outcomes following adverse events in childhood. The core analysis of the study will focus on investigating the trajectories of resilience across time and exploring its links with mental and physical health and other child characteristics. However, as the planned analysis is highly flexible and responsive to changes in the field, it is not possible to speculate meaningfully about this here, but all analyses will be registered on the Open Science Framework website prior to any analysis being conducted.

### Strengths of This Study

We believe this is one of the first longitudinal cohort studies exploring the factors associated with the development of emotional resilience in primary school-age children. In our measures, we also assess multiple risk and protective factors from individual traits (including cognitive information processing and lifestyle factors) to social and community resources. We also employ mixed methods, including quantitative and qualitative data, as well as experimental methods in cognitive tasks.

This provides a unique opportunity to understand the factors involved in the early stages of how resilience emerges and develops as well as the impact of these various factors over time. Our sample is also notable in being one that includes children growing up in socioeconomically deprived and marginalized communities. These children are not only typically underrepresented in mental health research, but they may also face multiple chronic stressors (poverty, housing difficulties, discrimination) where resilience—individual traits and external resources—are especially relevant in navigating these daily challenges. The flexible nature of the cohort measures allows us to respond to early findings and new information or data in the field as this is published.

### Weaknesses in This Study

This study relies heavily on self-report from young children, and it is not always clear how reliable or valid this method is in children of this age. We have tried to balance this by including measures by teachers and parents. However, parents are notoriously difficult to engage in this process, and this may result in lower levels of data from parents. Teachers also may be less responsive due to their many responsibilities and limited time to complete assessments. The large number of child assessments may also cause participant fatigue, particularly in a school setting. This may lead to nonrandom missingness in the results.

### Dissemination Plan

The results of this study will be published in academic journals and presented at academic conferences throughout the life of the project. We will also use the Youth Resilience Unit and the Unit for Social and Community Psychiatry social media accounts to further disseminate the research results. A brief debriefing report will be prepared for all participants, parents/carers, and schools, which will be circulated when the results have been prepared. Oral presentations of the key findings will also be offered to all participants, parents/carers, and schools.

All dissemination activities will draw on established research and clinical networks in our partners. Dissemination will be conducted with consideration of the safe data and safe statistical analysis protections. No individual level data will be published that could be linked back to a person or institution, and all output will be assessed to determine if there is a risk of disclosure through things such as single frequency counts in tables or identifying information in any qualitative fragments. In such cases, data will be censored, obscured, or changed to protect individual confidentiality. Where possible, any sensitive or difficult findings will be discussed with the participants or relevant institution if this is about a clinic or similar setting, prior to publication to avoid any inadvertent reputational harm or negative consequences of the findings being made public.

## Abbreviations

DEER: Development of Emotional Resilience
REDCap: Research Electronic Data Capture
